### Ethics and consent

Potential participants will be approached and given an introduction to the study and basic eligibility criteria required for participation. Participants who meet the eligibility criteria for language, age, PTB, treatment duration and mobile phone access will be given a consent form (Additional file 1) to sign before screening for alcohol and tobacco use eligibility as the alcohol-related questions are sensitive and the fieldworkers must access the patient treatment record. If recruited to the trial, participants will be ask to consent to enter the trial, including consent for audio recording of the MI counselling sessions (Additional file 1). A witness signature will be required where the participant is unable to read or write.

The identity of participants will be protected by allocating each participant a unique trial number, which will be used on all research documents and will ensure anonymity for the data analysis. Participation will be voluntary; participants will be informed of their right to withdraw from the study at any time without giving a reason for their withdrawal. The project is unlikely to be directly harmful to TB patients with the exception of inconvenience in terms of time spent on the counselling sessions. Participants will receive ZAR 60 (US$4.19) travel and other expenses reimbursement for each MI counselling session and follow-up visit related to the study.

### Timeline and procedures

Figure 1 Additional file 4 outlines the overall participant flow through the trial. Eligible and consenting patients will be enrolled in the trial and the baseline interviewer-administered questionnaire and record review completed. Participants will receive a baseline interview on the same day as the recruitment or on the nearest available date suitable to both the participant and the LHW. The initial part of the questionnaire covers socioeconomic and demographic factors. We will also assess for depression using the CES-D10 [38], a validated tool, as depression may be a potentially moderating or mediating factor affecting treatment outcome. See Additional file 2 for the full case report form (CRF).

**Fig. 1 Fig1:**
[figure not shown]
CONSORT Flow diagram outlining randomisation and participant recruitment

The next part will cover medical history, particularly TB and HIV history and current medications. Participants identified as current smokers at eligibility screening will be asked more in-depth about their smoking habits and quit history. All participants will be asked about their use of smokeless tobacco and exposure to second-hand smoke. Participants will also be asked about time and money spent on TB-related healthcare visits in the past three months and health-related quality of life (see the ‘Economic evaluation’ section). After administering the baseline interviews, fieldworkers will draw the allocation envelopes and organise the follow-up sessions for the participants. Each of the interviews on health status, tobacco and alcohol use at baseline, three months and six months is not expected to last > 25 min.

### Primary outcome

The primary outcome is TB treatment success at 6–9 months of follow-up, measured using the routinely collected programmatic TB treatment outcomes as defined by the World Health Organization (WHO) and adopted in South Africa. This is a binary variable defined as either successful treatment (cured or treatment completed) or failed treatment, death, acquired drug resistance, loss to follow-up or ‘default’, or not outcome evaluated. Table 1 defines the different treatment outcomes according to the South African Department of Health National Tuberculosis Management Guidelines [2].

**Table 1 Tab1:** Definitions for TB treatment outcomes according to the South African Department of Health National Tuberculosis Management Guidelines

Treatment outcome	Definition
Cure	Patient in whom baseline smear or culture was positive at beginning of treatment AND is smear/culture negative in the last month of treatment and on at least one previous occasion at least 30 days prior According to local protocol, a patient who is diagnosed using Gene Xpert and is sputum negative for TB at 11 and 23 weeks is considered ‘Cured’.
Treatment completed	Patient whose baseline smear or culture was positive at the beginning and has completed treatment but does not have a negative smear/culture in the last month of treatment and on at least one previous occasion > 30 days prior. Patients diagnosed with PTB whose baseline smear (or culture) result was negative and who started treatment based on clinical and radiological findings who have shown clinical improvement and completed the prescribed course of treatment. *N.B. The smear examination may not have been done or the results may not be available at the end of treatment.*
Treatment failure	Patient whose baseline smear or culture was positive and remains or becomes positive again at 5 months or later during treatment. Patients who were negative at baseline but were later found to be positive. *N.B. This definition excludes those patients who are diagnosed with RR-TB or MDR-TB during treatment.*
Died	Patient who dies for any reason during the course of TB treatment.
Treatment default	Patient whose treatment was interrupted for two consecutive months or more during the treatment period.
Transfer out	Patient who was referred to a facility in another district to continue treatment and for whom the treatment outcome is not known.
Acquired resistance	Participants who are subsequently referred for MDR treatment.

Individual TB treatment records will be used as the primary source of information. The TB treatment record is the routinely used clinical document initiated by the TB nurse when the patient first presents at the TB clinic and includes demographic information as well as a comprehensive overview of the patient’s treatment over time. The TB treatment outcomes will be obtained 6–9 months after the TB treatment start dates. This is to allow for short periods of treatment interruption and time needed to confirm the TB treatment outcomes status. For example, the TB nurse may have to wait for end of treatment TB sputum or culture results or time may be required to determine whether a participant died. In some cases, TB patients may also undergo a longer TB treatment regimen.

Routinely reported outcomes will be verified for correctness by checking the actual individual diagnosis and treatment records. For example: if the outcome is classified as cured, then the criteria for diagnosis and outcome definitions should have been adhered to. Attempts will be made to verify the information of patients classified as ‘defaulted’ or who are lost to follow-up by contacting them telephonically or sending them a short text message. Sputum cultures and smears will be performed at baseline, two months, three months and six months per routine care.

### Secondary outcomes

The following outcome measures will also be recorded at the six-month follow-up:sputum conversion at the end of treatment: this will be measured by negative culture or smears in the group of participants who had bacteriology confirmed PTB at baseline, i.e. cure rates in intervention group versus control group for participants who initially had sputum AFB-positive, culture-positive or GeneXpert-positive PTB;six-month continuous smoking abstinence: the Russell Standard defines continuous abstinence as a self-report of not smoking > 5 cigarettes from the start of the abstinence period (in this case, six months), supported by a negative biochemical test (exhaled carbon monoxide [CO] < 10 ppm) at final follow-up [39]. For the purpose of our study, we will, however, use a more stringent criterion of exhaled CO < 7 ppm, based on findings from our previous study that some participants who reported continued smoking had an exhaled CO < 10 ppm [26]. This analysis will be performed on the group of participants who were current tobacco smokers at baseline;reduction in harmful or hazardous drinking: alcohol use will be measured using the AUDIT questionnaire. The questionnaire will be administered at screening (which will take place on the same day or shortly after the baseline assessment) and again at three months and six months. Changes in the total AUDIT score will be used to compare change in drinking behaviour between control and intervention groups. This analysis will be performed on the group of participants who were harmful or hazardous drinkers at baseline.TB and ART medication adherence: adherence to both TB and ART medications will be measured using a modified version of the AIDS Clinical Trials Group (ACTG) Adherence Questionnaire. The questionnaire is a validated tool for measuring adherence specifically to ART and we will use an adapted version to also measure TB medication adherence [40]. Field workers will administer the baseline part of this questionnaire as part of the baseline CRF and adherence will be measured at both three months and six months.

Adherence will be measured using an adherence index calculated by the formula (using the four-day recall table):$$ \left[\mathrm{Total}\ \mathrm{number}\ \mathrm{of}\ \mathrm{doses}\ \mathrm{taken}/\mathrm{Total}\ \mathrm{number}\ \mathrm{of}\ \mathrm{doses}\ \mathrm{prescribed}\right]\ \mathrm{x}\ 100 $$

ART patients with at least 95% of adherence will be considered as having optimal adherence and those with < 95% will be considered as having low (or suboptimal) adherence. For the TB medication regimen, patients with at least 95% of adherence will be considered as having optimal adherence and those with < 95% will be considered as having low (or suboptimal) adherence:increase in proportion of HIV-positive participants on ART: HIV status will be recorded in the TB Treatment Record. HIV-positive participants will be asked about ART status at baseline, three months and six months using standardised questions on the CRF.

The following outcomes will be measured at three months:biochemically verified three-month sustained tobacco cessation;reduction in harmful or hazardous drinking;TB drug and ART adherence;increase in proportion of HIV-positive participants on ART.

The schedule for enrolment, intervention and assessments is presented in Fig. 2. Table 2 summarises the methods of data collection and analysis for each of the primary and secondary outcomes.

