**Methods:**

This is a prospective, multicentre, two-arm individual randomised controlled trial looking at the effectiveness and cost-effectiveness of a complex behavioural intervention (the ProLife programme) on improving TB and lifestyle-related outcomes in three provinces of South Africa. The ProLife programme consists of an MI counselling strategy, delivered by lay health workers, augmented with subsequent SMS. We aim to recruit 696 adult participants (aged 18 years and over) with drug-sensitive pulmonary TB who are current smokers and/or report harmful or hazardous alcohol use. Patients will be consecutively enrolled at 27 clinics in three different health districts in South Africa. Participants randomised individually to the intervention arm will receive three MI counselling sessions one month apart. Each MI session will be followed by twice-weekly SMS messages targeting treatment adherence, alcohol use and tobacco smoking, as appropriate. We will assess the effect on TB treatment success, using standard World Health Organization (WHO) treatment outcome definitions (primary outcome), as well as on a range of secondary outcomes including smoking cessation, reduction in alcohol use, and TB medication and anti-retroviral therapy adherence. Secondary outcomes will be measured at the three-month and six-month follow-ups.

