### Data collection and management

Data will be collected and recorded by field workers equipped with Android phones with a mobile data collection application installed. MI counselling and data collection will take place in a well-ventilated private area inside or outside the clinic (but within the grounds of the health facility); MI sessions will be audio-recorded where consent has been obtained. Fieldworkers and LHWs will be provided with high particulate respirator masks to minimise the risk of infection.

Fieldworkers will follow-up all participants in both arms at three and six months within a window period of two weeks before and two weeks after the ideal three-month and six-month visit. Participants will receive SMS reminders three days before each planned visit. Participants will also be in a position to send ‘please call me’ messages to the district coordinators, who will then call the participant to solve problems that may have arisen with the appointment.

The electronic data captured will be stored on secured and password-protected storage servers and mobile phones which ensure data privacy through only allowing authorised research staff access to the data. The electronic data collection system used for the study requires an SMS gateway to send and receive messages to the research participants. Consenting participants’ phone numbers, participant IDs and associated SMS messages will be stored on the SMS gateway’s secured and password-protected server.

Data quality will be ensured by providing fieldworkers with standard operating procedures (SOPs), training and ongoing support on the importance of data quality, data collection and data collection problem solving. Training will consist of a four-day session before the commencement of the pilot and a one-day training session focusing on problems identified during the pilot preceded the trial. The data manager will continuously monitor the captured data for missing variables and inconsistencies in order to resolve any data problems.

The data manager will export the data from the secured server, conceal the participants study arm allocation and de-identify the data before sharing the data in STATA and R compatible formats. The exported de-identified data will be stored in Dropbox, a secure cloud storage platform, for sharing with the lead trial statistician at the University of York for analysis.

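### End-of-treatment sputum conversion (cure) is recorded at six months, although the protocol itself allows 6–9 months to settle end-of-treatment status

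*Protocol article*

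**What the plan says.** Three places in the protocol article set the time of the secondary cure endpoint.

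- **Secondary outcomes** opens its list with "The following outcome measures will also be recorded at the six-month follow-up:sputum conversion at the end of treatment". It then explains the endpoint as "i.e. cure rates in intervention group versus control group for participants who initially had sputum AFB-positive, culture-positive or GeneXpert-positive PTB".
- **Abstract, Methods** gives the general rule: "Secondary outcomes will be measured at the three-month and six-month follow-ups".
- **Table 2** bases the cure comparison on sputum at baseline, 5 and 6 months. It analyses the comparison as a binary variable, cured or not cured, in participants positive at baseline.

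The section **Primary outcome** treats the same status differently. Success there means cured or treatment completed, and "The TB treatment outcomes will be obtained 6–9 months after the TB treatment start dates". The reason follows: "This is to allow for short periods of treatment interruption and time needed to confirm the TB treatment outcomes status". The first example given is that "the TB nurse may have to wait for end of treatment TB sputum or culture results", and longer regimens are mentioned as well. Table 1 ties cure to a negative smear or culture in the last month of treatment plus an earlier negative one. For patients diagnosed by GeneXpert, a local rule accepts negative sputum at 11 and 23 weeks.

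**The concern.** Cure is both a component of the primary outcome and the whole of this secondary endpoint, yet the two are given different reading times. The protocol supplies the argument against the earlier time itself. One of its reasons for waiting up to nine months, the late return of end-of-treatment sputum or culture results, concerns exactly the data that the secondary endpoint uses.

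Two things are at stake. First, one participant could be cured in the primary outcome and unresolved, or possibly not cured, in the secondary one, only because the second was read earlier. Second, being unresolved at six months is related to interruption of treatment. ProLife aims to improve adherence, so the unresolved share need not be equal in the two arms. The secondary comparison would then mix bacteriological cure with the speed of completing treatment.

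**Working it through.** **1. The plan's own figure.** The article gives no number for the cure endpoint. Its only design figure is for the primary outcome: 0.86 against 0.76, 80% power, two-sided 5%, 25% attrition.

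- Without continuity correction: n = [1.960·√(2·0.81·0.19) + 0.842·√(0.86·0.14 + 0.76·0.24)]² / 0.10² = 240.4, so 241 per arm.
- With continuity correction: n′ = (n/4)·[1 + √(1 + 4/(n·0.10))]² = 261 per arm.
- With attrition: 261/0.75 = 348 per arm, or 696 in total.

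This matches the stated size exactly. It rests on the primary outcome, so moving the secondary read-out does not change it.

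**2. Interrupted or prolonged course.** Assume for illustration a six-month course. The article does not state a course length, but it places the last routine sputum at six months.

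- Uninterrupted, the last month of treatment is month 5 to month 6.
- An interruption of k months moves it to month 5 + k to 6 + k. With k = 1 it runs from month 6 to month 7.
- At six months no last-month sample exists yet, so the general cure definition in Table 1 cannot be met.
- Table 1 counts default only from two consecutive months of interruption, so this participant is not a defaulter. Treatment ends at 7 months, inside the 6–9 month extraction, and the primary outcome can record cure.

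A longer regimen has the same effect.

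**3. Uninterrupted course under the local rule.** The second sample falls at 23 × 7 = 161 days. Six months is 182.6 days. A result returned within 182.6 − 161 = 21.6 days is therefore available at six months of treatment, and cure can be settled. For such participants the two reading times agree.

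**4. What a gap would do, under assumptions only.** The article gives no share of late finishers or pending results. Three assumptions are needed:

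- 0.86 and 0.76 stand in for the final cure rates (they are the article's treatment success rates);
- 261 participants per arm are evaluable, which is generous because only those positive at baseline count;
- a share u of eventual cures is unresolved at six months and coded as not cured, which the article does not say.

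The observed rate is then p·(1 − u). Power is for a two-sided 5% test without continuity correction.

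| u, both arms | Observed rates | Difference | Power |
|---|---|---|---|
| 0 | 0.860 vs 0.760 | 0.100 | 83% |
| 5% | 0.817 vs 0.722 | 0.095 | 73% |
| 10% | 0.774 vs 0.684 | 0.090 | 64% |
| 20% | 0.688 vs 0.608 | 0.080 | 48% |

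If u differs by arm:

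- 10% in the intervention arm and 5% in the control arm: 0.86·0.90 − 0.76·0.95 = 0.774 − 0.722 = 0.052.
- The reverse: 0.86·0.95 − 0.76·0.90 = 0.817 − 0.684 = 0.133.

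If unresolved cases are left out or imputed, none of these figures applies.

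**The case against.** The best defence is that the article is consistent if read kindly. The endpoint is named as an end-of-treatment one, and cure is a treatment outcome in Table 1. The Primary outcome section obtains the treatment outcomes, in the plural, at 6–9 months. On this reading the six-month follow-up is only a label for the final assessment, as opposed to the three-month list. The 5- and 6-month samples in Table 2 would be a sampling schedule, since the same samples also verify the primary outcome. This has some force, and it may be what the investigators intend. But the text attaches this endpoint to the six-month follow-up, the Abstract repeats the rule for all secondary outcomes, and nothing extends the reading for this one.

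Two stronger readings are tempting and do not stand.

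- A reader might infer that late finishers and pending results are counted as not cured. Table 2 names a binary variable, not a rule for unresolved cases. The Statistical analysis section provides for missing data, including multiple imputation, and the detailed coding may lie in an analysis plan that is not shown.
- A reader might also infer that an early visit, "within a window period of two weeks before and two weeks after the ideal three-month and six-month visit", cuts off the sputum result. That window is given for the fieldworkers' follow-up. Sputum is taken under routine care, and the TB treatment record is the main source for outcomes. The window therefore gives no estimate of how many participants would be misclassified. Even on a model with visits two weeks early, the first visit falls on day 168.6 of treatment, after the week-23 sample on day 161.

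**Conclusion.** The point holds as a conflict of reading times. Taken as written, the secondary cure endpoint is read at six months, and the protocol's own reasons show that this is too early for participants with interrupted or longer courses or with results pending. Their cure status can differ between the primary and the secondary outcome.

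The size is unknown. It may be near zero where courses are uninterrupted and results return quickly under the 11- and 23-week rule. It grows with interruptions, longer regimens and slow cultures, none of which the article quantifies. The figures in step 4 show only how sensitive the comparison would be under one possible coding.

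A reader might go further and expect a bias for or against ProLife. The document supports neither: the difference can shrink or grow, depending on which arm has more unresolved cures. The issue is confined to one secondary outcome, so it is worth correcting but does not threaten the main result.

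**What to change.** In Secondary outcomes and Table 2, take end-of-treatment sputum conversion (cure) from the same verified TB-record extraction as the primary outcome, at 6–9 months after treatment start. Use the sample from the last month of treatment and its final result. Keep the six-month visit for the interview- and CO-based outcomes. Amend the Abstract sentence so that it no longer ties every secondary outcome to the three- and six-month follow-ups.

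Reading the record is also better than imputing a cure status that the trial will itself extract within three months. The change is one of wording: the record is already extracted and checked at that time, so no visit, sample or participant is added. The one drawback is that this secondary outcome becomes available up to three months later.

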**Fig. 2 Fig2:**
[figure not shown]
SPIRIT Figure outlining data collection throughout trial

**Table 2 Tab2:** Summary of methods of data collection and analysis for primary and secondary outcomes

Variable	Method of data collection	Method of data analysis
Primary outcome: TB treatment outcome as defined by WHO and the South Africa TB Management Guidelines (see Table 1)	• CRF and TB treatment record • Treatment outcome as recorded by TB nurses in TB cards using the standard WHO definitions of cure, completions, failure, death, TB treatment interruption, drug resistance developed in course of treatment (confirmed for correctness by checking sputum culture/smear at baseline, at 5 and 6 months)	Binary outcome: successful (cured of completed) vs not successful (died, failure, treatment interruption, drug-resistant TB) All participants, excluding those transferred out
Secondary outcome: sputum conversion	• Sputum culture/smear at baseline, 5 and 6 months to determine cure rates for PTB patients who had a positive smear or culture at baseline • Sputum conversion at 2–3 months	Binary cured vs not cured for the subgroups of participants who had a positive smear/culture at baseline Binary conversion vs not for the subgroups of participants who had a positive smear/culture at baseline
Secondary outcome: change in smoking behaviour	• CRF – questions as per Russell’s Standard – baseline smoking behaviours and then at 3 and 6 months • Exhaled carbon monoxide reading at 3 and 6 months	Binary outcome validated 3 and 6 months sustained smoking cessation for the subgroup of participants who were smoking at baseline
Secondary outcome: percentage reduction in harmful or hazardous drinking (change in AUDIT score)	• AUDIT score at baseline and at 3 and 6 months	Change in AUDIT score (continuous) for subgroups of participants who were hazardous or harmful drinkers at baseline
Secondary outcome: HIV and TB medication adherence	• CRF – questions modified from ACTG	Binary outcome (% adherent vs non-adherent)
Secondary outcome: proportion of HIV-positive participants on ART	• HIV status at baseline • ART status at baseline, 3 months and 6 months	Binary on ART vs not on ART for the subgroup of HIV-positive participants, taking into account baseline % on ART

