### Statistical analysis

We will summarise baseline data descriptively by trial arm; however, we will not undertake statistical comparisons. For continuous measures, we will report means and standard deviations (SD); for skewed data, we will also provide medians and interquartile ranges. For categorical data, we will report counts and percentages. For the primary outcome, we will conduct analysis on an intention-to-treat basis. We will use binary logistic regression to compare the main outcome between the intervention and the usual care arm.

We will carry out similar analyses for the secondary outcomes with appropriate regression techniques: logistic regression for categorical outcomes and linear regression for continuous outcomes. We will also adjust for baseline characteristics and other covariates (HIV status, sex, alcohol versus tobacco versus both, district) if these differ between trial arms at baseline.

In case of missing data, we will employ a number of methods including multiple imputations to assess the sensitivity of the results. We will conduct subgroup analyses to determine whether TB treatment outcomes differ between subgroups, as follows: HIV-positive versus HIV-negative participants; participants with an alcohol problem only versus smokers only versus participants who are conjoint smokers and drinkers; and participants who were GeneXpert positive versus participants who were GeneXpert negative at baseline.

We will follow the CONSORT statement guidelines in reporting. We will use the statistical packages STATA and R to carry out the analyses and a *P* value < 0.05 will be considered as statistically significant. The statistical analysis pertaining to cost-effectiveness will be described in the section detailing the planned economic evaluation.

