We will estimate the cost per additional successful TB outcome by computing an incremental cost-effectiveness ratio (ICER) combining treatment and wider healthcare costs with outcome data from the trial. The analysis will also use measures of health utility. We have registered on the EuroQol website to use the country specific version of EQ-5D-3 L for South Africa to measure health-related quality of life at baseline, three-month and six-month follow-ups. We will use EQ-5D-3 L to estimate changes in quality-adjusted life years (QALY) using the area under the curve by using the utility score at each time point to create a profile [41]. A cost utility analysis is then performed by combining incremental health outcomes using QALYs with the incremental cost. The cost utility analysis will estimate the cost per QALY that estimates the value for money afforded by administering the ProLife intervention over and above usual care. We will plot incremental cost against incremental outcome using a cost-effectiveness plane. We will also conduct sensitivity analyses to assess the robustness of the ICER and use bootstrapping techniques to calculate cost-effectiveness acceptability curves. Supporting analysis will also present the costs to patients incurred by making visits to both trial arms to present the wider cost burden. However, these costs will not be included in the base case scenario as the objective is to present the value for money from the perspective of the purchaser or commissioner.

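### Drinking is analysed as change in AUDIT without a prespecified baseline AUDIT covariate, which costs precision (about 1% to 35% of variance, on assumed inputs) but does not bias the comparison

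*Protocol article*

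**What the plan says.** The Secondary outcomes section states: "Changes in the total AUDIT score will be used to compare change in drinking behaviour between control and intervention groups". The drinking row of Table 2 gives the same analysis, "Change in AUDIT score (continuous) for subgroups of participants who were hazardous or harmful drinkers at baseline", although the label of that row calls the outcome a percentage reduction. The collection column of the row reads "AUDIT score at baseline and at 3 and 6 months", so every participant in this analysis has a baseline score.

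The Statistical analysis section assigns "logistic regression for categorical outcomes and linear regression for continuous outcomes" to the secondary outcomes. Its covariate rule, which concerns differences seen before treatment, is: "We will also adjust for baseline characteristics and other covariates (HIV status, sex, alcohol versus tobacco versus both, district) if these differ between trial arms". The same section says that no statistical comparison of baseline data will be made.

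Elsewhere the baseline value is used explicitly: the row of Table 2 on antiretroviral therapy (ART) ends "taking into account baseline % on ART". The drinking row has no counterpart.

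**The concern.** Three things are settled in the article itself rather than left open: the outcome is a change, the model is linear, and covariates are conditional on observed imbalance. Together they leave the strongest candidate predictor of follow-up AUDIT, its own baseline value, without a guaranteed place in the model. AUDIT could come in under the general reference to baseline characteristics, but only once someone has looked at the arms. No criterion says what counts as a difference, and formal baseline comparison has been ruled out.

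At stake are the precision of one secondary estimate, its exposure to chance imbalance, and a model choice that depends on the data. Precision is already limited here: the analysis uses only part of the 696 participants, and that number was set for TB treatment success. The Table 2 label adds a smaller problem, since a percentage reduction and a mean change in points are different quantities.

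**Working it through.** **The plan's own figure.** The article gives no sample size, SD or correlation for AUDIT. Its only calculation is for the primary outcome: 0.76 versus 0.86, 80% power, significance level 0.05 (taken as two-sided), 25% attrition. The usual two-proportion formula gives 241 per arm, or 261 with continuity correction. Then 261/(1 − 0.25) = 348 per arm, or 696 in total, which matches the article. The present point does not affect that number. It supplies only the 261 evaluable participants per arm used in the illustration below.

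**Inputs for AUDIT.**
- From the article (Participants; Recruitment process): drinkers enter with a score of at least 8 (men) or 7 (women) and below 20.
- Assumed: r, the correlation of baseline with follow-up AUDIT, at 0.3, 0.5 and 0.7.
- Assumed: k, baseline SD divided by follow-up SD, at 1 (equal) and 0.6 (baseline spread narrowed by the entry limits).

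**Formulas**, in units of the follow-up variance:
- Unadjusted change score: 1 + k² − 2rk
- With a baseline term: 1 − r²
- Excess of the first over the second: (k − r)², which is never negative. In large samples a baseline term therefore cannot increase the residual variance.
- With k = 1 the ratio of adjusted to unadjusted variance is (1 − r²)/(2(1 − r)) = (1 + r)/2.

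| k | r | Change score | Baseline-adjusted | Reduction |
|---|---|---|---|---|
| 1 | 0.3 | 1.40 | 0.91 | 35% |
| 1 | 0.5 | 1.00 | 0.75 | 25% |
| 1 | 0.7 | 0.60 | 0.51 | 15% |
| 0.6 | 0.3 | 1.00 | 0.91 | 9% |
| 0.6 | 0.5 | 0.76 | 0.75 | 1% |
| 0.6 | 0.7 | 0.52 | 0.51 | 2% |

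**Chance imbalance.** A change score fixes the slope of follow-up on baseline at 1, whereas the actual slope is r/k. If the arms differ by one AUDIT point at baseline by chance, the expected change-score estimate is displaced by r/k − 1 points. That is −0.7, −0.5 and −0.3 for k = 1, and −0.5, −0.17 and +0.17 for k = 0.6. A baseline term estimates the slope and removes this displacement.

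**Illustrative power.** Suppose half of the 261 per arm are drinkers (about 130) and the true effect is 0.3 follow-up SDs; both are assumptions.
- k = 1: power rises from 53.5% to 71.9% (r = 0.3), from 67.8% to 79.9% (r = 0.5) and from 87.9% to 92.4% (r = 0.7).
- k = 0.6: power rises from 67.8% to 71.9%, from 79.4% to 79.9% and from 91.9% to 92.4%.

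**The case against.** The best defence is that nothing here is invalid. Both arms face the same entry thresholds, so the fall in scores expected from selecting on baseline is the same in each and cancels in the comparison. A reader might infer that regression to the mean biases the result; under randomisation it does not. This part of the defence stands in full.

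The defence can add that the article does not exclude baseline AUDIT. Defining the outcome as change does not prevent a baseline covariate: regressing change on arm and baseline gives the same arm effect as regressing the follow-up score on arm and baseline. The bracketed covariate list may also be only illustrative. This stands in part. It would be too strong to say that the plan forbids the term, but the only route the article offers is conditional on an observed difference.

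The size is also open to challenge. The 15% to 35% gain needs equal SDs, while the entry limits narrow the baseline spread and leave follow-up scores free. That is correct, and the lower rows of the table must be read alongside the upper ones. As for the Table 2 label, the same cell glosses it as change in AUDIT score, so the intended analysis can be identified and the correction is editorial.

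A reader might extend the point to the economic evaluation and infer that quality-adjusted life years (QALYs) will be compared without adjusting for baseline utility. The article does not support that. It says it will estimate "changes in quality-adjusted life years (QALY) using the area under the curve", which describes how the quantity is built. It states no regression model or covariates for the difference between arms, and a condensed article commonly leaves that to an analysis plan.

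**Conclusion.** The point holds as one of efficiency and prespecification in a single secondary outcome. The article fixes a change-score analysis and makes adjustment depend on observed imbalance, so baseline AUDIT has no guaranteed place although it is collected. The comparison remains unbiased. The avoidable variance is 15% to 35% for r from 0.7 down to 0.3 with equal SDs, but only about 1% to 9% if the baseline SD is about 0.6 of the follow-up SD. Neither r nor the SD ratio is in the article, so the true figure could lie anywhere in that span, and the loss may be small. The case for the change rests less on a particular gain than on three facts: in large samples it cannot increase the residual variance, it removes a data-dependent choice, and it costs almost nothing. The primary outcome and the sample size of 696 are untouched.

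**What to change.** In the analysis plan, and in the protocol at its next revision:

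1. State that AUDIT at three and at six months will be analysed by linear regression on arm with baseline AUDIT as a covariate, among participants who were hazardous or harmful drinkers at baseline, whatever imbalance is observed.
2. Report the adjusted mean difference in AUDIT points with its confidence interval. If change is kept as the dependent variable, the arm effect is identical as long as baseline AUDIT is in the model.
3. Reword the label of the drinking row in Table 2 so that it names this continuous outcome and not a percentage reduction.

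If an existing analysis plan already contains items 1 and 2, only the article's wording needs to be aligned. The cost is a few sentences: no new data, visits or participants are needed, because AUDIT is already recorded at screening, three months and six months.
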